### Statistical Analysis

#### Sample Size Considerations

The sample size calculation for the primary outcome (eHygiene—SUS) was based on the primary outcome of the SUS score from patients. Various studies [7,14,15] have used the SUS scale to assess the usability of a medical service or mHealth tool and reported mean SUS scores of 47.5-81.2 (SD 9.9-21.1). Since the patients in the eHygiene study are clustered by practice, we used a cluster randomized design calculation for the sample size calculation. Assuming the difference in the SUS score between the patient-evaluated eHygiene model and other published mHealth tools has a mean of 8 and an SD of 10, a sample size of 72 patients from 12 practices (6 per practice) will achieve 90% power, at an alpha of .05. Considering the potential dropout rate, a sample size of 144 patients will satisfy the statistical power of the primary outcome.

Dentists and dental hygienists will complete the SUS for each patient when the dentist and hygienist complete an eHygiene visit, which means each dentist and hygienist will evaluate the eHygiene model 12 times. Assuming a mean difference of 30 (SD 20) between the first and last patients evaluated by the dentists and hygienists, using a paired *t* test, a sample of 7 dentists or hygienists will achieve 90% power, at an alpha of .05. Considering potential dropouts, recruiting 12 dentists and 12 dental hygienists will achieve satisfactory statistical power for this aim.

Using a cluster randomized design to calculate the sample size for the primary outcome of DPC and assuming a mean difference in the patient-evaluated DPC score between the current hygiene model and the eHygiene model of 8 (SD 10), a sample size of 48 patients from 12 practices (4 per practice) will achieve 85% power, at an alpha of .05. A sample size of 144 patients will satisfy the statistical power of the DPC outcome, while considering potential dropouts.

For the sample size calculation of the tertiary outcome (SELFIE), we expect to reach data saturation [16] (no new themes are identified) after conducting 12 individual tests. The sample size was determined based on previously published studies, where between 6 and 11 usability tests were conducted to assess technology products, for instance, smartphone app usability [17,18].

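### The sample-size section calls both patient SUS and patient DPC the primary outcome, each at alpha .05, and the article does not say which one is the headline or how they are judged together

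*Protocol article*

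**What the plan says.** All the conflicting text is in the Sample Size Considerations section of the protocol article.

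- The section opens with patient SUS: "The sample size calculation for the primary outcome (eHygiene—SUS) was based on the primary outcome of the SUS score from patients". The assumed difference is "between the patient-evaluated eHygiene model and other published mHealth tools has a mean of 8 and an SD of 10", and the stated result is "a sample size of 72 patients from 12 practices (6 per practice) will achieve 90% power, at an alpha of .05".
- The third paragraph gives DPC the same rank: "Using a cluster randomized design to calculate the sample size for the primary outcome of DPC". The assumed difference is "between the current hygiene model and the eHygiene model of 8 (SD 10", and the stated result is "a sample size of 48 patients from 12 practices (4 per practice) will achieve 85% power, at an alpha of .05".
- The last paragraph moves to a third rank: "For the sample size calculation of the tertiary outcome (SELFIE". No outcome in the article is called secondary.

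Table 1 lists SUS and DPC together under Aim 1 without rank. The section on analyses for Aim 1 treats them in parallel, also without rank and without a joint success rule. The Introduction describes the study as a hypothesis-generating pilot.

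**The concern.** Two outcomes carry the label primary, each with its own effect size, power and alpha of .05. Either the DPC label is a slip, or there are two primary outcomes and the rule for judging them together is not stated.

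The label matters when the results are written up. Suppose SUS shows nothing and DPC shows a difference. Under one reading of the section the study missed its primary outcome; under the other it met one of two. Both readings can be defended from the text, so the choice could be made after the data are seen. If either result may serve as the primary one, the overall false-positive rate is also no longer the 5% attached to each calculation.

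**Working it through.** **Inputs from the article (Sample Size Considerations).** SUS: difference 8, SD 10, 72 patients, 6 per practice, 90% power, alpha .05. DPC: difference 8, SD 10, 48 patients, 4 per practice, 85% power, alpha .05. The article does not give the intracluster correlation (ICC), the sidedness of the tests, or the correlation between SUS and DPC. Two-sided tests are assumed below.

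**1. The plan's own power figures.** Without an ICC they cannot be confirmed. The two-group cluster formula with k practices per group and m patients per practice is SE = SD × √(2 × (1 + (m − 1) × ICC) / (k × m)). With k = 12 per group and a back-fitted ICC of 0.24:

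- SUS: SE = 10 × √(2 × 2.20 / 72) = 2.472; 8 / 2.472 = 3.236; power = Φ(3.236 − 1.960) = 89.9%.
- DPC: SE = 10 × √(2 × 1.72 / 48) = 2.677; 8 / 2.677 = 2.988; power = Φ(2.988 − 1.960) = 84.8%.

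Both stated powers are matched, but only with 12 practices in each of two groups, whereas the study has 12 practices in all. The ICC was chosen to fit. The error-rate check in steps 2 and 3 uses neither the ICC nor the sample sizes.

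**2. Error rate if either outcome may count.** With independent tests at .05 each, the chance of at least one false positive is 1 − 0.95² = 9.75%. Both scores come from the same patients, so some positive correlation is plausible. For two-sided tests with bivariate normal test statistics of correlation ρ, the chance is 1 − P(|Z₁| < 1.96 and |Z₂| < 1.96):

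| ρ (assumed) | Chance of at least one false positive |
|---|---|
| 0 | 9.75% |
| 0.3 | 9.5% |
| 0.5 | 9.1% |
| 0.7 | 8.3% |
| 0.9 | 7.0% |
| 1.0 | 5.0% |

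**3. Error rate under other rules.** If both outcomes must succeed, the error is at most 5%. That maximum is approached when one null hypothesis is true and the other outcome is almost certain to succeed. With one sole primary outcome it is 5%.

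**4. Is an alpha split a cheap alternative?** Not clearly. Take the planned 144 patients as two groups of 72, in 6 practices each with 12 patients per practice, at the same assumed ICC of 0.24. The effective size per group is 72 / (1 + 11 × 0.24) = 72 / 3.64 = 19.8, and 0.8 × √(19.8 / 2) = 2.516. Power at alpha .025 is Φ(2.516 − 2.241) = 61%, against Φ(2.516 − 1.960) = 71% at .05. On a one-group reading with an assumed ICC of 0.10, power at .025 stays above 99%. The cost of a split therefore depends on a design reading and an ICC that the article does not state.

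**The case against.** The strongest reply is that this is not a confirmatory trial. The Introduction calls it a hypothesis-generating pilot. The analyses for Aim 1 plan scores, comparisons between practices and models of influencing factors. They name no test of SUS against published tools or of DPC against the current hygiene model, which are the two differences used for sizing. Power figures justify a sample size; they do not by themselves create a confirmatory claim. This stands, and it moves the weight from the error rate to the reading of the results.

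A second reply is that the ranks may follow the aims. SUS and DPC both belong to Aim 1, Aim 2 has no sample-size calculation, and SELFIE is Aim 3, called exploratory in the Abstract. That would explain why no secondary outcome appears in the section. It is a coherent reading, but the article does not state it. It would also leave two primary outcomes without a rule for judging them together.

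A third reply is that multiplicity methods commonly sit in an analysis plan, which is not shown. That is fair, and the lack of an adjustment method is not the point here. The article itself says which outcome is primary, and says it in two ways.

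A reader might infer that the plan carries a false-positive rate close to 10%. The documents do not support that. The figure needs nearly uncorrelated tests and a rule that either success counts, and the article states neither.

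**Conclusion.** The inconsistency is real and can be checked within one section: two outcomes share the primary label, each sized at alpha .05, with no ranking and no joint rule. The main consequence is that the headline outcome is not fixed before the data are seen.

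The effect on error rate is conditional. It rises above 5% only if either result may count as primary, and then depends on a correlation that the article does not give; 9.75% is the ceiling. In a study that calls itself hypothesis-generating this is a correction worth making before results are reported, not a threat to the design.

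**What to change.** In Sample Size Considerations, keep patient SUS as the sole primary outcome at alpha .05, as the opening sentence has it. Change the DPC label to secondary and say that DPC is interpreted after SUS, in fixed sequence. Table 1 carries no ranks and needs no change.

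The cost is about one sentence of wording. SUS keeps its full alpha, and neither the sample size nor the data collection changes. The one thing given up is that DPC can no longer stand in as the primary result if SUS is null.

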#### Analyses for Aim 1: eHygiene

We will calculate SUS scores for the eHygiene model (post-eHygiene SUS) as rated by patients, dentists, and dental hygienists. The SUS score from the patients and DHCPs between practices will be compared. A linear mixed effects model will be used to examine factors that influence the SUS score as perceived by patients, including patient factors (demographic, socioeconomic, education, profession, and experience with using a digital device and mHealth tools) and DHCP factors (demographic and dental practice experience), while considering the clustering effects within practices and providers. The eHygiene SUS score as rated by dentists and dental hygienists from treating the first patient through the last study patient will be compared to assess whether the DHCP-determined SUS score is associated with a learning curve.

We will calculate the DPC score as rated by patients, which assesses how well the patients understand the planned treatment and the quality of the communication between the patients and dentists who participate in eHygiene. We will use a linear mixed effects model to examine factors that influence the DPC score perceived by patients, including patient factors (demographic, socioeconomic, education, profession, and experience with using a digital device and mHealth tools), DHCP factors (demographic and dental practicing experience), and time spent on the eHygiene visit, while controlling for the clustering effects within practices and providers. We will run separate models for patients and DHCP.

Regarding qualitative data, the interviews will be standardized using interview guides, audio-recorded, transcribed, coded, and analyzed for thematic content. The audio recordings will be transcribed by the Temi (San Francisco, CA) transcription service and further verified by 2 trained research personnel. Transcribed data will be analyzed using MAXQDA software (VERBI GmbH, Berlin, Germany). The data will be coded by 2 trained coders with predetermined open codes using a codebook with a description of the coding tree. Thematic content will be further analyzed using categorizing and contextualizing strategies to understand the factors associated with acceptance of and barriers to eHygiene among patients and DHCPs.

#### Analyses for Aim 2: Economic Impact

We will conduct analysis for the following parameters: (1) PPE consumption and estimated cost and comparison between eHygiene and traditional hygiene examination models for each practice; (2) eHygiene chair time per study patient, learning curve–related fluctuations in chair time per practice, and comparisons between practices; (3) eHygiene virtual visit time and comparison between practices; and (4) DHCP (dentist and dental hygienist) personnel cost related to eHygiene in-office and virtual visits, compared with traditional hygiene examination visits.

#### Analysis for Aim 3: SELFIE Intraoral Photos

Parameters to be evaluated include time spent on photo taking, number of photos, and readable photos by a dentist evaluator using a photo assessment from (Multimedia Appendix 6). Factors including patient demographic, education, and experience with using a digital device and mHealth tools that potentially relate to patient capability will be further assessed.

The “think-aloud” videos recorded during the SELFIE sessions will be reviewed by a trained study evaluator to analyze common themes of challenges patients encounter, using a SELFIE assessment form (Multimedia Appendix 7). The key tasks are connecting cameras with a tablet, locating the photo-taking module in the TeleDent software, using a cheek retractor, taking front-view and posterior teeth photos, and ensuring photos are stored in the TeleDent software. User performance for these key tasks will be ranked as critical (requiring assistance to proceed), severe (major delay and/or frustration), or cosmetic (minor) and annotated to the specific task. Based on rankings, the team will suggest changes to the instructional video and clinic procedures for future implementation.

## Results

The study has been peer-reviewed and funded by the US National Institute of Dental and Craniofacial Research. This study received single institutional review board approval from the University of Alabama at Birmingham (#300006506) and local context review from the University of Rochester (#6077). The eHygiene study is expected to launch in August 2021. Data collection and analysis are expected to conclude by December 2021 and March 2022, respectively.

## Discussion

### Study Innovation

This study is innovative in several ways. First, conducting virtual dental examinations (the mDent model) using intraoral photos and x-rays is novel and potentially transformative to dental practice. Using smartphones and mobile devices to take photos of the mouth and teeth and conduct oral disease screening has been recently reported [19-21]; however, the feasibility of engaging dental hygienists and patients to obtain intraoral images using an intraoral camera has not been assessed. Second, transforming the traditional one-on-one tactile dentist examination to an eHygiene visit requires a team effort from several stakeholders: the patient, dental hygienist, and dentist. This level of teamwork in dental offices is innovative. The team effort could lead to better DHCP-patient communication and a better understanding and compliance with this approach to dental treatment. Third, integrating the mHealth concept into dentistry to achieve population-wide oral health screening and monitoring is extremely innovative and offers a vehicle to promote patient-engaged oral health education and patient-driven early detection of oral disease. Fourth, the eHygiene model is a novel way of preserving PPE during the COVID-19 and other respiratory-transmissible disease outbreaks.

### Impact on Clinical Practice

Successful completion of this eHygiene pilot study will provide data on the acceptance and economic impact of virtual dental examinations during eHygiene visits, which will be a test vehicle for the future mDent model. The results will inform potential immediate modification of the dental service system to provide better safety and preserve PPE amid COVID-19 and other infectious disease outbreaks and beyond.

## Appendix

Multimedia Appendix 1 Intraoral photo taking template.

Multimedia Appendix 2 Dentist role-specific questionnaire.

Multimedia Appendix 3 Hygienist role-specific questionnaire.

Multimedia Appendix 4 Patient role-specific questionnaire.

Multimedia Appendix 5 Qualitative interview guide.

Multimedia Appendix 6 SELFIE session intraoral images assessment form.

Multimedia Appendix 7 SELFIE session video assessment form.

## Abbreviations

DHCP: dental health care personnel
DPC: dentist-patient communication
GD: general dentist
mDent: mobile dentistry
mHealth: mobile health
NIDCR: National Institute of Dental and Craniofacial Research
PPE: personal protective equipment
SUS: System Usability Scale
